### Hypotheses

Our hypotheses are as follows:Morning, as compared to evening, administration of warfarin will produce a more consistent anticoagulant effect and improve the proportion of time a patient spends in the target therapeutic INR range (TTR = time in therapeutic range).A less variable day-to-day dietary vitamin K consumption at dinner, whether consistently high or consistently low, will reduce variability in the anticoagulant effect of warfarin and improve the proportion of time a patient spends in the target therapeutic INR range.

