### Aims

This study has the following aims:To determine (by RCT) whether switching current warfarin users from evening to morning dosing will alter the proportion of time spent in the therapeutic INR rangeTo determine (by cross-sectional analysis of baseline data) whether evening warfarin users with greater variability in daily dinnertime vitamin K ingestion have a lower time in the therapeutic INR rangeTo determine by prospective subgroup analysis of RCT data whether the effect of warfarin timing on TTR (i.e., the effect of changing to morning dosing) is influenced by day-to-day variability in vitamin K consumption.

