#### Primary outcome

The primary outcome is percentage change in time spent *outside* the family physician’s target INR range for that patient. This primary outcome has been chosen because we believe this is a measure more likely to be shared by patients across a wide range of TTR. It is also the time spent outside of range that contributes more directly to risk of thrombosis and hemorrhage; hence, the change in this measure is more clinically meaningful than the change in TTR itself.

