#### RCT

All analyses will be by intention to treat. The primary analysis of percentage change in time outside of therapeutic range will be by Student’s *t* test if the data appear to be normally distributed or by Mann-Whitney U test if they are not. As percentage change in time outside of therapeutic range can only be calculated for patients for whom the time outside normal range is not zero, this analysis will exclude anyone who was in range 100 % of the time at baseline. The secondary analyses will be by Student’s *t* test or Mann-Whitney U test (for percentage change in TTR, maximum and minimum INR values, and percentage of time spent above and below target range) and by Student’s *t* test or Fisher’s exact test (for both percentages of patients with TTR >75 % and <60 %, and major warfarin-related cardiovascular events). A subgroup analysis of the influence on the intervention of the numbers of days per week that high vitamin K foods are ingested will be carried out looking at an ANOVA analysis of percent change in time outside of therapeutic range according to three possible categories for the number of days per week of consumption of high vitamin K-containing foods (these being less than 2, 2 to 5, and greater than 5 days per week). In the same analysis we will also examine the effect on the intervention of the patient’s global assessment of how variable their consumption of high vitamin K containing foods is. To do this, we will convert the 4-point scale of possible responses into a dichotomous variable that combines the two options indicating the most variable diet and the two options indicating the least variable diet.

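### Aim 3 asks about effect modification on TTR, but the only planned effect-modification analysis uses percent change in time outside range, a different scale that cannot include every patient

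*Protocol article*

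**What the plan says.** The third aim (Protocol article, Aims), to be met by a subgroup analysis within the trial, is to find out "whether the effect of warfarin timing on TTR (i.e., the effect of changing to morning dosing) is influenced by day-to-day variability in vitamin K consumption". The endpoint named there is TTR.

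The matching analysis is in Statistical analysis, RCT. It is a subgroup analysis "looking at an ANOVA analysis of percent change in time outside of therapeutic range according to three possible categories" of weekly intake of high vitamin K foods. The patient's own rating of diet variability, which is the modifier Aim 3 names, enters the same model: "In the same analysis we will also examine the effect on the intervention of the patient’s global assessment". Both modifiers are therefore tested on percent change in time outside range.

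The same section notes that this variable "can only be calculated for patients for whom the time outside normal range is not zero", and says of the primary analysis that "this analysis will exclude anyone who was in range 100 % of the time at baseline".

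TTR appears elsewhere in the plan, but not for this purpose. Change in TTR is a secondary outcome compared between arms. The multiple regression under Baseline cross-sectional analysis uses baseline TTR and serves Aim 2.

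**The concern.** The aim and its analysis use different measures. For one patient the difference looks harmless, because time in range and time out of range add to 100 % and always move in opposite directions. Effect modification is a comparison between groups, however, and there a ratio to each patient's own baseline and an absolute proportion of time can give different answers.

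They agree if baseline time out of range is the same in the diet groups. The protocol expects otherwise: Hypothesis 2 holds that a less variable dinner intake of vitamin K "will reduce variability in the anticoagulant effect of warfarin and improve the proportion of time a patient spends in the target therapeutic INR range", and Aim 2 looks for that difference at baseline. On the trial's own premise, the denominator of the percent change differs by the very factor being tested as a modifier.

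At stake is whether the trial reports an answer to the question Aim 3 poses, namely who gains more time in range. As written, it reports an answer on another scale, in a population without the best-controlled patients.

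**Working it through.** **Plan's own figure.** The protocol gives no figure for Aim 3. Its sample size for the primary outcome reproduces: n per group = 2 × (1.960 + 1.282)² × (40/20)² = 84.1, rounded up to 85. The exact t-test solution is 85.03. The 20 % target and the 40 % SD are reused below.

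**Assumptions.** The protocol gives no baseline TTR and no INR variance. Every baseline below is assumed.

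**1. Equal relative effect.** TTR gain in points = baseline time out of range × relative reduction. With the plan's 20 %:
- baseline 30 %: 0.20 × 30 = 6 points
- baseline 40 %: 0.20 × 40 = 8 points

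Percent change shows no effect modification; TTR shows a 2-point difference.

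**2. Equal absolute effect.** Percent change = gain / baseline. With 7 points in both groups:
- baseline 25 %: 7/25 = 28 % reduction
- baseline 45 %: 7/45 = 16 % reduction

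TTR shows no effect modification; percent change shows a 12-point difference. If the baselines are only 3 points apart (27 % and 30 %), the reductions are 26 % and 23 %, which is trivial.

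**3. Opposite order.** Take baseline 20 % with a 30 % relative reduction, against baseline 40 % with a 20 % reduction. The TTR gains are 6 and 8 points. Percent change favours the first group and TTR the second. This pattern needs unequal baselines and a larger relative effect where the baseline is lower.

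**4. Means and small baselines.** Suppose one patient goes from 5 % to 15 % out of range and another from 60 % to 30 %. The percent changes are +200 % and −50 %, mean +75 % (worse). The TTR changes are −10 and +30 points, mean +10 points (better). An ANOVA compares means, so it is exposed to this.

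**5. Simulated INR series.** Inputs, all assumed: range 2–3; 7, 10 or 14 tests per window; lag-1 correlation 0.2; SD of patient means 0.15; median within-patient SD 0.42 (consistent diet) or 0.62 (variable diet) with log-normal spread 0.35; linear interpolation; morning dosing cuts the INR SD by 15 % in everyone.

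| | Consistent diet | Variable diet |
|---|---|---|
| Baseline time out of range | about 22 % | about 36 % |
| TTR gain, points | 5.1–5.3 | 6.3–6.5 |
| Arm difference in median percent change | −27 to −29 | −19 to −20 |
| Not calculable (baseline zero) | 9–21 % | 1–6 % |

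The order of the groups differs between the two scales. These are medians. The SD of percent change, which governs a comparison of means, ran mostly into the thousands of percent because a few baselines lie close to zero. A coarser model (12 in-or-out readings per period, so no baseline between 0 and 1/12) gave SDs of 69–92 %. The size of the problem therefore depends on how near to zero baselines fall.

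**6. Scale against exclusion.** In the coarser model, with 20 % out of range and a 40 % reduction against 50 % and a 30 % reduction, dropping zero baselines removed 28 % and 3 % of patients. The TTR contrast narrowed from 7.1 points (15.0 − 7.9) to 5.0 (15.3 − 10.3) and did not reverse. The change of scale drives any reversal; the exclusion adds distortion.

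**7. Precision.** Assume 200 patients in four equal arm-by-diet cells of 50. The standard error of the interaction is SD × √(4/50). With the plan's SD of 40 % it is 11.3 points; with an assumed TTR SD of 20 points it is 5.7. The contrasts in step 5 are about 8–9 points of percent change (0.7–0.8 standard errors) and about 1.2 TTR points (0.2 standard errors).

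**The case against.** Running a subgroup analysis on the primary outcome is ordinary practice. Aim 1 is also worded in terms of time in range, although its primary outcome is percent change in time outside range, so the Aims may use TTR loosely for INR stability. The Primary outcome section gives a reason for the relative measure: "the change in this measure is more clinically meaningful than the change in TTR itself". That reason could extend to asking who benefits. This stands in part, and rewording Aim 3 would also reconcile the text. But the reason is given for the primary outcome, and Aim 1 keeps change in TTR as a secondary comparison. Aim 3 has no TTR counterpart.

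Interaction depends on scale, and this objection stands in full. In the simulation morning dosing acts identically on INR variability in both groups, and the TTR difference comes from baseline alone. A reader might infer that the planned analysis would answer Aim 3 wrongly or name the wrong diet group. The documents do not support that, because it treats the absolute scale as the truth.

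A reader might also infer that the direction will reverse. The simulated reversal rests on an assumed baseline gap of about 15 points and on medians, whereas the plan specifies ANOVA, and it lies below one standard error.

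Nor do the documents show that the excluded patients come mainly from consistent-diet groups. Hypothesis 2 gives a direction for diet variability only, and none for the three intake-frequency categories. The exclusion sentence is written for the primary analysis. It reaches the subgroup analysis because the same variable is undefined at a zero baseline.

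**Conclusion.** The point holds as a mismatch between aim and analysis. Aim 3 names TTR, and no arm-by-diet analysis of TTR is planned. The measure used instead has three drawbacks for this question: it is relative to a baseline that the protocol expects to differ by diet variability, it is undefined for patients fully in range at baseline, and its mean is unstable when baselines are small.

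On size, the same 20 % relative reduction is 6 against 8 TTR points if baselines are 30 % and 40 %. The discrepancy shrinks towards nothing as the baselines converge. These baselines are assumptions. Reversal of direction is a possibility and not a forecast, and with 200 patients neither scale would reliably separate the diet groups if effects were as simulated. The sample size and the primary comparison are unaffected. The change is still worth making, because it is cheap and lets Aim 3 be answered on the endpoint it names.

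**What to change.** In the RCT part of the statistical analysis, specify for Aim 3 a model of follow-up TTR, adjusted for baseline TTR, with arm, diet measure and their interaction. Fit it in all randomised patients with follow-up INRs, including those fully in range at baseline. Keep percent change in time out of range as a labelled supportive analysis on the primary-outcome scale, state how many patients in each diet group it leaves out, and describe both results as exploratory.

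The cost is one or two sentences. No new data are needed, since TTR is already calculated for the secondary outcomes. The small downside is that the main Aim 3 result is no longer on the primary outcome's scale, which is why both should be reported.

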#### Baseline cross-sectional analysis

The effect on baseline TTR of the number of days per week that high vitamin K-containing foods are consumed will be analyzed with multiple linear regression using baseline covariates which include: gender, age ≥80 years, hospitalization in the last 6 months, temporary planned discontinuation of warfarin in the last 6 months, number of daily prescription medications, <6 months of warfarin use, each of the three possible categories for number of days per week consuming high vitamin K-containing foods, and the patient’s dichotomous global assessment of how variable their pattern of vitamin K consumption is.

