## Background

Vitamin K is obtained primarily from green leafy vegetables (in particular kale, spinach, chard, beet greens, broccoli, cabbage, romaine lettuce, and Brussels sprouts) [1]. It is an essential cofactor used by the liver to “activate” the clotting factors it releases into the blood. Vitamin K has a very short half-life in the body (approximately 2 ½ hours) and cycles through an active (so far as its ability to “activate” clotting factors) and inactive form in the liver [2]. Warfarin acts by preventing one of the intermediary steps necessary to convert the inactive form of vitamin K back to the active form and hence it reduces the amount of available activated clotting factor [1]. When vitamin K is first ingested, however, it is in an easily activated form upon which warfarin has little effect [2]. As a result, consumption of high vitamin K-containing foods can counteract the effect of warfarin, and highly variable consumption of these foods may cause clinically important INR variability in some individuals [3].

The effectiveness of the anticoagulant warfarin is measured by the international normalized ratio (INR) blood test, which indicates how long it takes the user’s blood to clot compared to normal [1]. Canadian warfarin users typically have their INR measured by their family physician every 1–4 weeks, and same-day changes in warfarin dosing are made in response to that day’s INR test. In order to shorten the response time for making a dosing change, patients are traditionally advised to have their INR test in the morning and to take their warfarin in the evening (so that the INR test result will be back in time to change that day’s warfarin dose if needed). However, this leads to taking warfarin at the same time of day as the most highly variable consumption of vitamin K. Conceivably, if warfarin activity is greater around the time of ingestion, when liver concentrations would be highest, taking warfarin in the morning (when the vitamin K content of typical breakfast foods is consistently low) might lead to greater stability in anticoagulant effect. The question of whether the time of ingestion of warfarin matters to INR stability has never been formally addressed.

We are conducting a pragmatic randomized controlled trial (RCT) of morning versus evening warfarin ingestion to determine whether the timing of warfarin ingestion matters to the stability of its anticoagulant effect.

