### Recruitment

Participating community family physicians in the Canadian provinces of British Columbia and Alberta will send a letter of invitation to all warfarin-using patients under their care with the exception of those whom they view as palliative or deemed incapable of informed consent. This letter: (1) describes the project, (2) lets patients know their physician’s office is participating, and (3) provides a central contact number that reaches our study coordinator for more information if they are interested. The study coordinator dialogs with interested patients who call in, screens them for eligibility, and obtains written informed consent (via online REDCap survey or mail-in consent form) from all patients willing to be randomized. For consenting participants who meet the screening criteria for eligibility, the family physician will be asked to provide investigators with the participant’s target INR range and their last 6 months of INR results, test dates, and warfarin dosing.

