### Randomization and allocation

Upon receiving eligible baseline INR data, consented eligible participants are contacted by a study coordinator via telephone to obtain baseline information presumed to be predictive of TTR. This includes age ≥80 years, hospitalization in the last 6 months, temporary planned discontinuation of warfarin in the last 6 months (e.g., for elective surgery), number of daily prescription medications, <6 months of warfarin use, the self-reported average number of days per week in which high vitamin K-containing foods are consumed, and how variable the participant feels this estimated level of vitamin K consumption is (on a 4-point scale). This study coordinator (who has no clinical patient interactions) then randomizes the participant, using the REDCap^TM^ randomization module to ensure allocation concealment, to intervention or control [5]. Randomization will employ variable blocks of 2 or 4 and will be stratified by the proportion of baseline INR readings within the therapeutic range (<50 %, 50–80 %, >80 %).

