### Sample size

We wish to be able to demonstrate a 20 % reduction in time out of therapeutic range and will conservatively estimate (since there are no prior studies exploring this outcome to guide us) that the standard deviation of this measure is twice the mean effect (i.e., SD = 40 %). For a *t* test with 1:1 allocation to the control and experimental groups, power = 0.9, alpha = 0.05, minimum difference = 20 %, and SD = 40 %, the required sample size per group is 85 (i.e., 170 subjects in total). Providing for potential dropouts, we will increase our target enrollment to 200 subjects.

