### Statistical analysis

#### Calculating TTR

The therapeutic INR range for each patient will vary and be determined by the treating physician. Typically the therapeutic range is 1 unit wide (often 2–3 or 2.5–3.5), but some physicians will choose narrower or wider ranges (e.g., 3.0–3.5 or 2–3.5). We will standardize the width of all target ranges by determining the midpoint of each patient’s individual target range and use upper and lower limits that are 0.5 unit above and below this midpoint. For example, if a physician is targeting a narrower than normal 3.0–3.5 range, we will use a midpoint of 3.25 and assume a (standardized width) target therapeutic range of 2.75–3.75. The proportion of time both in and out of therapeutic range will be determined using the linear interpolation method of Rosendaal, which (conceptually) draws a line between sequential INR values no more than 8 weeks apart and assigns a projected INR value to every day in that interval [8].

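### The Aim 2 regression adjusts for age only as ≥80 years and names no allowance for patients who share a family physician, so age confounding can remain and standard errors can be somewhat too small.

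*Protocol article*

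**What the plan says.** The section on the baseline cross-sectional analysis names one model for Aim 2. The effect of vitamin K food intake on baseline TTR "will be analyzed with multiple linear regression using baseline covariates which include: gender, age ≥80 years, hospitalization in the last 6 months", followed by planned warfarin interruption, number of prescription medications, under 6 months of warfarin use, the three intake categories and the dichotomised diet variability. All of these are measured on the patient. No physician or clinic term appears, and no variance that allows for grouping.

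Randomization and allocation lists the baseline items collected by telephone "to obtain baseline information presumed to be predictive of TTR". Age has the same form there: "This includes age ≥80 years".

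Other sections show how patients are grouped:
- Recruitment: each participating physician "will send a letter of invitation to all warfarin-using patients under their care", apart from those viewed as palliative or incapable of consent.
- Background: "Canadian warfarin users typically have their INR measured by their family physician every 1–4 weeks", with dose changes made the same day.
- Calculating TTR: "The therapeutic INR range for each patient will vary and be determined by the treating physician". The width of the range is then standardised to 0.5 unit either side of its midpoint.

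The number of physicians, the patients per physician, the ICCs and the age distribution are not given.

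**The concern.** Aim 2 is a cross-sectional comparison of patients with different diets. Randomisation does not balance those groups, so the covariate list is the main protection against confounding. A single cut at 80 treats a patient of 55 and one of 79 as the same age. If age is linked to both vitamin K intake and INR control, part of that link stays in the diet coefficient.

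Patients of one physician also share testing and dosing habits, so their TTRs are plausibly correlated. If their diets are correlated too, ordinary regression overstates the information in the sample. The interval for the diet effect is then too narrow. The second hypothesis of the trial rests on this analysis.

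**Working it through.** **The plan's own figure.** The only power calculation is for the randomised comparison ("power = 0.9, alpha = 0.05, minimum difference = 20 %, and SD = 40" per cent). The two-sided normal formula gives 2 × (1.960 + 1.282)² × (40/20)² = 84.06, rounded up to 85 per group. The exact t-test solution is 85.03. Then 170/0.85 = 200. The stated figures reproduce, but they say nothing about Aim 2. Everything below rests on assumed ranges.

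**Age.** For normal ages with mean μ and SD σ, let z = (80 − μ)/σ, and let p be the share aged 80 or over. The squared correlation between age and the indicator is φ(z)²/[p(1 − p)].

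| Mean / SD | z | p | Variance of age captured |
|---|---|---|---|
| 70 / 10 | 1.00 | 0.159 | 0.44 |
| 70 / 12 | 0.83 | 0.202 | 0.49 |
| 75 / 10 | 0.50 | 0.309 | 0.58 |
| 75 / 12 | 0.42 | 0.339 | 0.60 |

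Worked for the first row: 0.242²/(0.159 × 0.841) = 0.44. About 40–56 % of the variance of age is therefore not adjusted for. Among patients under 80, an age SD of roughly 7–9 years remains. This measures the information lost. It is not a bias in TTR points, which would need the slopes of TTR and diet on age.

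**Shared physician.** The exposure is each patient's own diet, so with m patients per physician the variance inflation is 1 + (m − 1) × ICC(TTR) × ICC(diet). The ratio of true to ordinary standard error is its square root, r. The actual error of a nominal 5 % test is 2 × [1 − Φ(1.96/r)].

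| m | ICC TTR | ICC diet | Inflation | r | Actual error |
|---|---|---|---|---|---|
| any | any | 0 | 1 | 1.00 | 5.0 % |
| 2 | 0.05 | 0.05 | 1.0025 | 1.00 | 5.0 % |
| 4 | 0.10 | 0.10 | 1.03 | 1.015 | 5.3 % |
| 10 | 0.10 | 0.10 | 1.09 | 1.04 | 6.0 % |
| 10 | 0.15 | 0.20 | 1.27 | 1.13 | 8.2 % |
| 10 | 0.20 | 0.20 | 1.36 | 1.17 | 9.3 % |
| 20 | 0.20 | 0.20 | 1.76 | 1.33 | 14 % |

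A simulation with 200 patients agrees: r = 1.15 and error 9.1 % for 20 physicians with 10 patients each and both ICCs 0.20, and r = 1.00 when diet does not cluster (TTR ICC 0.20). At r = 1.13 the ordinary standard error falls short of the true one by 1 − 1/1.127 = 11 %.

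**The case against.** The strongest reply is that the clustering part is an omission. The covariate list opens with a word that does not close it. Handling of grouped patients in a secondary observational aim is commonly left to an analysis plan, which is not shown here. That stands, and it limits this part to a recommendation. It does not touch age, whose coding the article fixes in two places.

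The article also standardises the width of every target range, which removes the mechanical effect of a physician's chosen width on TTR. That stands too, but differences in test interval and dose adjustment remain.

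A third reply is that age in years is only a preference over a cut at 80, since nothing shows that age relates to diet. It is fair that no bias is demonstrated. The loss of information follows from the coding itself, however, and in an unrandomised comparison there is no gain to set against it.

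A reader might go further and infer that the interval is too narrow, or that the physician confounds the diet effect by managing INR closely and also advising a steady diet. The documents support neither. They do not say that physicians advise on diet, and without clustering of diet the standard error is correct. Even under assumptions chosen to show such confounding (both ICCs 0.10, physician-level correlation 0.3, TTR SD 22 points, an even diet split with SD 0.5, 200 patients), the bias is 0.3 × 0.10 × 22/0.5 = 1.3 TTR points. The standard error is 22/(0.5 × √200) = 3.1.

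**Conclusion.** The point holds in a limited form and is minor. The firm part is age: the plan fixes a cut that captures only about 44–60 % of the variance of age under the assumed distributions, in an analysis that depends on covariate adjustment. Residual age confounding is possible. It is not shown, because it needs age to be related to both diet and TTR.

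The clustering part is conditional. For 2–10 patients per physician, TTR ICC 0.05–0.15 and diet ICC 0.05–0.20, the true standard error is 1.00–1.13 times the ordinary one, and the upper end needs every assumption at its highest value. Larger groups with stronger clustering would give more.

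None of this should be read as a fault in the randomised comparison, which does not use this model.

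**What to change.** 1. In Randomization and allocation, record age in years. In Baseline cross-sectional analysis, replace the ≥80 indicator by a continuous term for age (linear plus quadratic, or a spline).
2. For Aim 2, report robust standard errors clustered on family physician, with a small-sample correction if physicians are few. These also cover the unequal precision of baseline TTRs, which under the inclusion criteria may rest on four INRs over 3 months or on a longer series.
3. Report a within-physician estimate as a sensitivity analysis.

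A random intercept for physician would not replace item 3, because it assumes that physician effects are unrelated to diet. With both ICCs equal to 0.10, the share of a physician-level bias that it keeps is 1/[1 + 0.10(m − 1)]: 1/1.1 = 91 % at m = 2, 1/1.3 = 77 % at m = 4 and 1/1.9 = 53 % at m = 10.

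Costs: the physician is already known, because the INR records come from that practice. Recruitment has begun, so age in years must be obtained for enrolled patients if only the yes/no answer was kept. The main interval may widen slightly. The within-physician estimate is less precise: with equal ICCs its standard error is larger by a factor of √[m/(m − 1)], about 1.41 at m = 2 and 1.15 at m = 4.
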